## Abstract

**Background:**

Diabetes prevention programs focus on people with prediabetes because they have a greater risk of developing type 2 diabetes mellitus than people with normal blood glucose levels. Weight management can reduce this risk. However, in our largely sedentary society, there is less enthusiasm for regular exercise. Whole-body electromyostimulation (WB-EMS) is a training technology that provides exercise-like effects by inducing muscle contractions using electrical currents. There is evidence that local EMS can improve glucose metabolism. Several studies investigated the effect of WB-EMS on cardiometabolic risk factors including blood glucose control in a population of individuals with metabolic syndrome. However, to the best of our knowledge, there is no randomized controlled trial examining the preliminary efficacy of WB-EMS on hemoglobin A_1c_ (HbA_1c_) levels in individuals with prediabetes.

**Objective:**

The objective of this randomized controlled trial is to pilot procedures for a randomized controlled trial testing WB-EMS training on glycemic changes in sedentary adults with prediabetes.

**Methods:**

A total of 60 community-dwelling sedentary adults aged 40-65 years with prediabetes will be randomized to one of 3 arms: WB-EMS + an activity tracker and a lifestyle education program (LEP) focusing on diabetes prevention, an activity tracker and LEP, or LEP only, with 20 individuals in each arm. The WB-EMS training will consist of 1.5×20 minutes per week. The intervention will last 16 weeks. As a pilot study, our main outcomes concern the number of participants who will be recruited, and comply with intervention and follow-up. The primary efficacy outcome of interest includes hemoglobin A_1c_. The intention-to-treat analysis will be conducted with the objective of providing CI estimation of treatment effects.

**Results:**

The recruitment of study participants started in February 2024. At the time of submission of this protocol for publication, the recruitment was still ongoing. As of October 2024, a total of 42 participants were allocated to the study groups. The anticipated date of recruitment completion is July 2025.

**Conclusions:**

The results of this trial will provide valuable evidence for future investigations comparing the efficacy of the WB-EMS intervention with traditional exercise training to improve glycemic control in this population.

**Trial Registration:**

ClinicalTrials.gov NCT06188481; https://clinicaltrials.gov/study/NCT06188481

**International Registered Report Identifier (IRRID):**

DERR1-10.2196/68761

## Introduction

### Overview

Type 2 diabetes mellitus (T2DM) is a serious and widespread disease and is recognized as a major public health challenge worldwide. According to the International Diabetes Federation (IDF), the current estimate of adults aged 20-79 years living with diabetes equals 9.3% (463 million) and is projected to increase to 10.9% (700 million) by 2045 [1]. As the prevalence of T2DM increases, effective prevention measures are increasingly important. Focusing on those who are at high risk of developing T2DM is a pivotal starting point.

A state of glucose metabolism is called prediabetes when diabetes mellitus is not yet present but elevated fasting plasma glucose levels or impaired glucose tolerance are known [2]. Hemoglobin A_1c_ (HbA_1c_) levels between 5.7% and 6.4% are indicative of prediabetes. The prevalence of prediabetes in Germany is estimated to be 26% in people aged 45 to 64 years and 31% in people aged 65 to 69 years [3]. Similarly, in the United States, 21.7% of people have prediabetes according to the HbA_1c_ diagnostic criteria [4]. The clinical relevance of prediabetes is that there is a significantly increased risk of developing T2DM compared to the normoglycemic population, which in turn is associated with an increased risk of developing cardiovascular disease, kidney disease, cancer, depression, and dementia [2]. The results from the population-based Rotterdam Study suggest that up to 74% of 45-year-olds with prediabetes will develop T2DM during their lifetime [5].

The results from the KORA-F4 study (Cooperative Health Research in the Region of Augsburg) and the SHIP-TREND study (Study of Health in Pomerania) suggest that up to one-third of people with prediabetes can be classified as physically inactive [6]. Lifestyle changes, such as physical activity and weight management, are of critical importance in preventing the development and progression of T2DM [2,7].

Although, physical activity interventions have shown beneficial effects on oral glucose tolerance, fasting glucose, and HbA_1c_ levels in people with prediabetes [8], insufficient physical activity in people with T2DM and prediabetes remains an issue in these populations [9]. There are several barriers associated with participation and long-term adherence to exercise programs among physically inactive people with diabetes, including lack of time, lack of motivation, poorer (self-rated) health, risk of injury, and social and environmental barriers [10]. Therefore, physical activity programs with an attractive profile are needed to reduce sedentary behavior and increase adherence to physical activity. A potential approach to achieve this goal is an innovative training technology called whole-body electromyostimulation (WB-EMS). WB-EMS provides exercise-like effects by inducing muscle contractions using electrical currents from an external source. WB-EMS simultaneously stimulates up to 8-12 major muscle groups with up to 2800 cm^2^ of electrode area. Electrodes are placed on the gluteus muscle, thighs, lower back, upper back, latissimus dorsi, abdomen, chest, and upper arms, and each body region is stimulated with an individualized pulse intensity while individuals perform low-intensity functional exercises in a standing position [11].

In recent years, WB-EMS has found its way not only into therapeutic training but also into rapid and widespread distribution, particularly in Europe, with more than 2000 commercial WB-EMS providers serving approximately 250,000 clients in Germany alone [12]. Due to its increasing popularity, time efficiency, ease of implementation, joint-friendliness, and personalized application, WB-EMS is increasingly the subject of scientific research. In fact, several studies have demonstrated positive effects of WB-EMS on muscle hypertrophy and body composition [13,14]. In addition, high adherence to the intervention and low dropout rates were reported previously [14]. Therefore, this training technology can be considered a promising approach when aiming to increase physical activity in a population of sedentary adults.

A nonrandomized study of WB-EMS showed benefits to HbA_1c_ levels and fasting glucose in middle-aged and older men with T2DM [15]. In addition, several small studies have shown that local EMS has beneficial effects on glycemic control [16]. In contrast, a recent randomized crossover study by Holzer et al [17] found no significant short-term difference in the acute postprandial glucose response between exercise with and without WB-EMS. However, due to the small sample size (6 patients with T2DM) and short intervention duration (three 20-min sessions), the results of this study cannot be generalized [17]. Some studies further investigated the effect of WB-EMS in a population of individuals with metabolic syndrome. While prediabetes and metabolic syndrome share some common characteristics, people with metabolic syndrome have heterogeneous cardiometabolic profiles, where prediabetes or elevated blood sugar levels might be present, but do not necessarily occur. A study showed that 12 weeks of regular WB-EMS in combination with nutritional counseling had a beneficial effect on body weight and composition, and positively affected blood cholesterol levels, but not HbA_1c_ levels [18].

A recent randomized controlled study investigated the effect of WB-EMS in comparison to resistance training on cardiometabolic risk factors. The study found that there was no significant effect on variables including HbA_1c_ [19].

We intend to use WB-EMS focusing on HbA_1c_ in people with prediabetes and then examine its preliminary efficacy. Therefore, an appropriate design is needed to compare the HbA_1c_ of the intervention group (IG) with that of the comparison groups.

### Study Objectives

Our main objective is to pilot the feasibility of a randomized trial testing WB-EMS for HbA_1c_ levels in people with prediabetes. The primary objective is to provide an estimation of the preliminary efficacy of the intervention on glycemic control in a sedentary group of adults with prediabetes compared with control groups (CGs).

The secondary objectives are to assess the preliminary efficacy of:

WB-EMS training on the individual's biomarkers (eg, triglycerides, high-density lipoprotein, and low-density lipoprotein).WB-EMS training on body composition, blood pressure, and heart rate.WB-EMS on other outcomes, such as quality of life and stress.

## Methods

### Study Design and Setting

The trial is designed as a randomized controlled pilot trial in a parallel design with 3 arms. The trial will be conducted at the Department of Population-Based Medicine at the University Hospital of Tübingen, Germany.

### Study Population

The study population will be selected on the basis of the following inclusion and exclusion criteria (Textbox 1).

Inclusion and exclusion criteria.
**Inclusion criteria**
Community-dwelling sedentary men and women aged 40-65 years without type 2 diabetes mellitusElevated hemoglobin A_1c_ levels (5.7%-6.4%)Not functionally impaired (Short Physical Performance Battery ≥10)Signed informed consentConsent to use the whole-body electromyostimulation and activity tracker
**Exclusion criteria**
High-grade arrhythmia, cardiac pacemaker carriers, heart failure, nephropathyCognitive impairmentType 2 diabetes mellitus

### Study Procedure

Figure 1 illustrates the study procedure. Screening of participants will take place in 2 stages (telephone prescreening and on-site screening). During the telephone pre-screening, the study staff will check key study eligibility criteria and inform participants about the study activities. If they are interested, they will be invited to the on-site screening. During the on-site screening, the study staff will perform the HbA_1c_ measurement. Furthermore, physical examination (eg, blood pressure) and detailed medical history will be collected to account for any possible contraindications and to ensure safe participation in the training program.

The final determination of eligibility to participate in the trial will take place after the screening. The participants will be randomized to 1 IG and 2 CGs. The duration of the intervention will be 16 weeks. At the end of the intervention period, individuals will return to the study site for a follow-up assessment. The participants of the IG will have a second follow-up assessment after 32 weeks.

**Figure 1 figure1:**
[figure not shown]
Flowchart of the study procedure. T2DM: type 2 diabetes mellitus; WB-EMS: whole-body electromyostimulation.

### Sample Size

The study population will consist of 60 individuals with 20 individuals in each study group. As this is a pilot study, no formal power analysis has been carried out. However, the target sample size was based on recruitment for 15 months at an estimated rate of 4 patients per month (ie, 60 patients), which was considered adequate to obtain reasonably reliable sample size estimates [20-22].

### Recruitment

Participants will be recruited through newspaper and social media advertisements. Flyers and posters will also be distributed to local doctors’ offices, pharmacies, hospitals, community centers, and self-help groups.

### Randomization, Blinding, and Concealment of Allocation

Eligible participants will be allocated to the study groups by computerized block randomization. This will be performed by an independent trial statistician. Neither the participants nor the researchers will know their allocation in advance. The participants will be strictly separated after randomization. The study staff will prevent participants from different study groups from arriving at the study site at the same time by planning study visits accordingly.

The blinding strategy focuses on study assistants and outcome assessors who will be blinded to the participants’ group status. All data analysts will also be blinded to group allocation.

### Intervention

The main intervention will be WB-EMS using equipment that has EU (European Union) medical device approval (miha bodytec, Type II). This equipment allows the simultaneous stimulation of up to 12 muscle groups (eg, thigh and upper arm, gluteal region, abdomen, chest, lower back, and upper back) with a total stimulation area of approximately 2800 cm^2^. The participants will receive the functional training underwear recommended by the manufacturer (water-absorbent cotton or elastane mix), over which a vest (upper body) and belts (upper arms, thigh, and gluteus muscle) are individually adjusted before each session. The system allows the intensity to be adjusted for each region (Figure 2). We will use an impulse protocol and exercise setting that has been evaluated in recent studies focusing on total and regional muscle mass [13], body fat [23], and physical function [13] in older cohorts. Furthermore, we designed low-intensity exercises to minimize the effect of voluntary movements themselves as low as possible.

A bipolar electric current with a frequency of 85 Hz and an impulse width of 350 microseconds is used in an interval approach with 6 seconds of EMS stimulation with a direct impulse boost and 4 seconds of rest. During the 6-second stimulation period, low-effort movements are performed in a standing position. The intensity of the EMS will be regulated on the basis of the individual’s reported Rating of Perceived Exertion (RPE) and the Borg Category Ratio Scale (Borg-CR10) [14]. We will use RPE to generate and maintain a sufficient but tolerable intensity of EMS application. After 4 weeks of conditioning at a lower pulse intensity, participants will be encouraged to increase the intensity. The impulse intensity will be adjusted individually for each body region in close interaction with the participant. During the session, the instructors will increase the intensity slightly every 3 minutes in close cooperation with the participants in order to maintain the target RPE (6-7) during the session. We will use a personal training setting with one certified and experienced instructor responsible for a maximum of 2 participants. The training will adhere to the requirements of the international EMS guidelines [24].

**Figure 2 figure2:**
[figure not shown]
Whole-body electromyostimulation.

### Study Groups

#### Intervention Group

The participants in the IG will train following a supervised and guided WB-EMS program 1.5 times per week (eg, every Monday or Tuesday and every other Thursday or Friday) for 16 weeks. The duration of each training session will be 20 minutes. Each session will include a 3-minute warm-up, a 15-minute main workout, and a 2-minute cool-down. In addition, participants will be asked to wear an activity tracker on their wrist for the entire 16-week study period and to participate in the lifestyle education program.

#### Control Groups

A total of 2 CGs are planned for the study. One CG will receive both the activity tracker to measure daily steps and the evidence-based lifestyle education program. The other CG will receive the lifestyle education program only.

#### Activity Tracker

The activity tracker (vivosmart 5, Garmin) will be used for self-monitoring of daily steps. Activity trackers may improve physical activity independent of the intervention (eg, people can monitor their daily steps) [25]. Therefore, it is important to include 2 CGs: one with the activity tracker to isolate the net effect of the WB-EMS intervention and one without the activity tracker.

#### Lifestyle Education Program

The evidence-based lifestyle education program consists of six 20-minute sessions that focus on lifestyle factors and diabetes prevention. The aim of the program is to provide education, information, and advice to prevent disease progression and improve quality of life and mobility. The education program includes topics such as the basics of healthy nutrition patterns, meal planning, the importance of physical activity, and stress management. Participants will receive recorded videos on each topic to ensure standardization of the content. To assess compliance, the participants will be followed up by the study staff, who will ask, whether the program was completed, or reminded to complete the program, in case of noncompliance.

#### Outcome Measures

The assessments described below will be performed at baseline (day 1) and after the 16-week intervention period. IG participants will also be assessed at 32 weeks. The timetable of the assessments is presented in Table 1. All measurements will be performed by the same research assistant, using identically calibrated equipment, in the exact same environment and at approximately the same time of day (±90 min).

**Table 1 table1:** Table1. Timetable of study procedure and assessments.

		Study period				
		Enrollment	Allocation (day 0)	Intervention (weeks 1-16)	Follow-ups	
					Week 16	Week 32
Eligibility screening		✓				
Informed consent		✓				
Review inclusion and exclusion criteria		✓				
Allocation			✓			
**Assessments**						
	HbA_1c_^a^ assessment	✓			✓	✓
	Lipid and cholesterol profile		✓		✓	✓
	Blood pressure		✓		✓	✓
	Hand grip strength		✓		✓	✓
	Body composition		✓		✓	✓
	Waist circumference		✓		✓	✓
	Questionnaires (WHOQOL-BREF^b^, SFI^c^, PSS-10^d^, PHQ-9^e^)		✓		✓	✓
**Interventions**						
	WB-EMS^f^, activity tracker and evidence-based lifestyle education program			WB-EMS 1.5/wk Activity tracker 6 x 20 min LEP^g^		
	Activity tracker and evidence-based lifestyle education program			6 x 20 min LEP Activity tracker		
	Evidence-based lifestyle education program			6 × 20 min LEP		

^a^HbA_1c_: hemoglobin A_1c_.

^b^WHOQOL-BREF: WHO Health-Related Quality of Life.

^c^SFI: Secure Flourish Index.

^d^PSS: Perceived Stress Scale.

^e^PHQ: Patient Health Questionnaire.

^f^WB-EMS: whole-body electromyostimulation.

^g^LEP: lifestyle education program.

#### Primary Outcome

As a pilot study, our main outcome is to assess the feasibility of the proposed intervention, with specific attention to the recruitment, adherence, and completion rates of the follow-up assessments. The prespecified primary outcome measure will be HbA_1c_ levels. A blood sample (capillary blood) will be collected via the finger stick technique. There is no need for the participants to fast prior to blood measurement. The sample will be analyzed according to the manufacturer’s instructions using Cobas b 101 system 2.0 (Roche Diagnostics).

#### Secondary Outcomes

##### Cardiometabolic Parameters

Changes from baseline in the levels of triglycerides, total cholesterol as well as high-density lipoprotein and low-density lipoprotein cholesterol will be assessed in capillary blood. A blood sample will be collected with the finger stick technique. The sample will be analyzed according to the manufacturer’s instructions using Cobas b 101 system 2.0 (Roche Diagnostics).

Waist circumference will be measured with a standard tape measure around the abdomen between the distal end of the rib cage and the top of the iliac crest along the horizontal plane (World Health Organization [WHO] guidelines).

In addition, changes in systolic and diastolic blood pressure as well as in heart rate will be investigated (boso medicux X, BOSCH + SOHN). The measurements will be performed in the sitting position after a short resting period of at least 5 minutes.

Body composition: Body mass and composition will be measured by direct segmental, multifrequency bioimpedance technique (InBody 770). This device measures the impedance of the trunk, arms, and legs separately using a tetrapolar 8-point tactile electrode system that applies 6 frequencies (1, 5, 50, 250, 500, and 1000 kHz).

##### Muscle Strength

Hand grip strength will be measured using a hydraulic hand dynamometer SAEHAN SH5001 (SAEHAN Corporation). The dynamometer grip width will be adjusted individually to the participant’s hand size. Tests will be performed in an upright standing position, arms down by the side. The standardized instruction to the participants will be consistently “squeeze as strongly as possible.” Three tests intermitted by 20 seconds of rest will be performed for the dominant hand and the average value will be used for the evaluation.

##### Stress

A self-reported questionnaire Perceived Stress Scale consisting of 10 questions about stress (PSS-10) will be used [26]. In each question, individuals are asked how often they feel a certain way on a 5-point scale from 1 for “never” to 5 for “very often.” The PSS score indicates levels of perceived stress, whereby higher scores indicate higher stress levels.

##### Depressive Symptoms

The Patient Health Questionnaire which consists of 9 questions on depressive symptoms (PHQ-9) is a standardized and validated self-reported questionnaire. It will be used to assess for changes from baseline regarding the presence and severity of such symptoms. The possible score ranges from 0 (no depression) to 27 (severe depression) [27].

##### Health-Related Quality of Life

The standardized and validated questionnaire WHO Health-Related Quality of Life (WHOQOL-BREF) consisting of 26 questions on general quality of life will be used [28]. This self-reported tool includes 4 domains: physical health, psychological health, social relationships, and environmental health. It also contains items about quality of life and general health. Each item of the WHOQOL-BREF is scored from 1 to 5 on a 5-point Likert scale. The scores are then transformed linearly to a 0-100 scale. A higher score indicates a higher quality of life.

##### Well-Being

Changes from baseline in self-reported well-being will be evaluated with the standardized and validated questionnaire Secure Flourish Index (SFI), which consists of 12 questions on general well-being. Each of the questions is assessed on a scale of 0-10. The SFI score is obtained by summing the scores from the 12 questions and results in a score from 0 to 120 [29].

### Baseline Characteristics

Table 1 describes the type of data and variables that are collected at various stages of the project. Furthermore, the following demographic and descriptive data are collected at the baseline assessment: gender, age, height (cm), medical history (diseases, surgery, and medicine consumption), physical activity (type, frequency, and duration), educational level, and employment status.

Trainers will monitor adverse events by asking participants if they have experienced any health problems (eg, physical injury and muscle soreness) since the last session. The research team will monitor any adverse events that may occur during participation in this study.

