## Results

The recruitment of participants and on-site screening started at the beginning of February 2024. At the time of submission of this protocol for publication, the recruitment was still ongoing. As of October 2024, a total of 169 individuals have registered for the study. Of these, 76 individuals were invited to attend the on-site screening, and the rest were excluded during the telephone prescreening process. Finally, 47 participants were eligible and 42 of those were randomized and allocated to the study groups. The 16-week intervention phase starts in groups of at least 6 participants (block randomization) in order to ensure randomized allocation to the 3 study groups. The use of sealed opaque envelopes ensured that neither participants nor researchers were aware of the allocation prior to the study (ie, allocation concealment).

The study is still in progress, and thus far, no adverse events have been recorded. The anticipated date of recruitment completion is of July 2025.

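### Adverse events are actively asked about at every WB-EMS session, with no matching question described for the control arms, so a by-arm tabulation would tend to inflate WB-EMS rates

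*Protocol article*

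**What the plan says.** The article's account of adverse events is two sentences at the end of the Baseline Characteristics section. The first gives a method: "Trainers will monitor adverse events by asking participants if they have experienced any health problems". Injury and soreness are its examples, and it looks back to the previous session. The second gives a responsibility: "The research team will monitor any adverse events that may occur during participation in this study". It is not limited to any arm, and it names no question, form or timing.

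Training sessions belong to one arm. Under Intervention Group: "The participants in the IG will train following a supervised and guided WB-EMS program 1.5 times per week", for 16 weeks. Under Intervention, the supervision is described: "We will use a personal training setting with one certified and experienced instructor responsible for a maximum of 2 participants".

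The control arms have no such sessions. Under Control Groups: "One CG will receive both the activity tracker to measure daily steps and the evidence-based lifestyle education program". The other control arm receives the education programme alone. The Lifestyle Education Program section says the content is delivered as recorded videos. It describes one staff contact: "To assess compliance, the participants will be followed up by the study staff", who ask about completion and remind those who have not complied. No health question is mentioned there.

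Table 1 lists assessments at enrolment, allocation, week 16 and week 32, with no row for adverse events. Study Procedure and Outcome Measures give the week-32 assessment to the intervention group only.

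**The concern.** The one elicitation method that is spelled out is attached to a procedure that only one randomised arm receives. Everyday complaints such as a sore back or a minor injury occur in all arms. If they are asked about every few days in one arm, and by an unstated route in the others, more will be recorded in the first arm even when the true rates are equal.

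This matters because the trial exists to pilot procedures for a definitive randomised trial. Events collected in a three-arm randomised study will be read by arm, whether or not a formal comparison was planned. An unequal questioning rule that is carried into the larger trial would distort its harms data in a predictable direction.

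**Working it through.** No figure in the article is challenged on this point. The check sets the contact schedules side by side and then shows how far the result depends on what is not stated.

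**Inputs from the article**
- WB-EMS sessions: 1.5 per week for 16 weeks (Intervention Group).
- Arm size: 20 (Sample Size; 15 months × 4 per month = 60 = 3 × 20).
- Visits after baseline: week 16 in all arms; week 32 in the intervention group only (Outcome Measures, Table 1).
- Education-programme contacts: number and timing not given.

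**Described active questions over 16 weeks**
- WB-EMS: 1.5 × 16 = 24 sessions, so up to 24 questions per participant and up to 24 × 20 = 480 in the arm. The question looks back to the previous session, so the first session may not count; hence "up to" in sense, not an exact total.
- Tracker plus education: none described.
- Education only: none described.
- Average look-back at a session: 112 days / 24 ≈ 4.7 days.
- Follow-up window: 32 weeks for WB-EMS, 16 weeks for each control arm.

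**Effect of the second sentence.** Research-team monitoring is not restricted to an arm. On the text, it applies to WB-EMS participants as well, so it adds to the trainer questions in that arm and does not offset them. Detection is then at least as high in WB-EMS as in the control arms, provided trainers record what they hear.

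**Illustration (assumptions, not in the article).** Let the true proportion with an event be p in every arm, with detection d₁ under session questioning and d₀ under research-team monitoring alone.

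Apparent ratio = (p × d₁) / (p × d₀) = d₁ / d₀, which does not depend on p.

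Take d₁ = 0.9 and 20 participants per arm:

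| d₀ | Ratio | Expected counts, p = 20% | Expected counts, p = 40% |
|---|---|---|---|
| 0.2 | 0.9 / 0.2 = 4.5 | 3.6 v 0.8 | 7.2 v 1.6 |
| 0.5 | 0.9 / 0.5 = 1.8 | 3.6 v 2.0 | 7.2 v 4.0 |
| 0.9 | 0.9 / 0.9 = 1.0 | 3.6 v 3.6 | 7.2 v 7.2 |

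The bias runs from none to large. Where it falls is decided by the research team's method, which the article does not state.

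**The case against.** The strongest reply has three parts.

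First, controls are not outside adverse-event monitoring. The research team covers everyone, and the article does not say that it merely waits for reports. This stands. It is not established that control-arm monitoring is passive, or that rates cannot be compared. What remains is that the one described question is tied to one arm and nothing described balances it.

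Second, this is a condensed article. Ethical Considerations refers to an approved protocol version that is not shown, and scripts and contact schedules commonly sit there. This limits the point but does not remove it. The article does more than omit detail: it states a collection rule, and that rule is unequal by arm.

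Third, adverse events are not among the objectives or the listed outcomes, and Statistical Analysis plans no between-arm comparison of them. The feasibility outcomes and the HbA1c estimate are unaffected. This stands, and it governs how serious the point is.

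A reader might also go further and take the interim statement in Results, "The study is still in progress, and thus far, no adverse events have been recorded", as a sign of under-recording, because muscle soreness is one of the things trainers ask about and 42 people had been randomised. The documents do not support that. They give neither the number who had started WB-EMS nor the sessions completed, and they do not say that every report of soreness is classed as an adverse event. A confidence limit around zero events would not help either: it measures small-sample imprecision, not unequal ascertainment.

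**Conclusion.** The point holds in a limited form. As the article is written, adverse events are solicited up to 24 times per participant in the WB-EMS arm. No solicited question is described for either control arm, and only the WB-EMS arm has follow-up beyond week 16. A raw tabulation by arm would therefore tend to overstate WB-EMS event rates relative to control. The size cannot be fixed from the documents; under the detection rates assumed above, the apparent ratio lies between 1.0 and 4.5 with no true difference.

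This rests on two readings. One is that control participants have no contact with the trainers, which follows from the description of the arms but is not stated outright. The other is that research-team monitoring is no more intensive in the control arms than in the WB-EMS arm.

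It is an inexpensive improvement, not an essential correction. Safety is not a listed outcome and no planned estimate changes.

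**What to change.** 1. Put the same scripted health-problem question, with the same look-back period, to all three arms at the common week-16 visit, and add an adverse-event row to Table 1.
2. Use the education-programme contacts as well only if they are set at the same times in every arm. At present their timing is not given, and reminders depend on non-compliance, so contact may differ between participants.
3. Protect the blinding described under Randomization, Blinding, and Concealment of Allocation. Use a self-completed form, or have the question asked by staff who are not blinded outcome assessors, because an answer about muscle soreness could reveal allocation.
4. Base any between-arm adverse-event table on those answers only. Report trainer-elicited session events and week-32 events separately, as WB-EMS-arm data. For participants already past week 16 when the change is made, show them as not asked.
5. State in a sentence how the research team's monitoring works in each arm.

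The cost is a little staff time and a short protocol note. The price in information is a coarser recall period for the comparative table: 16 weeks if only the week-16 visit is used, against about 4.7 days on average at sessions. Minor events will be missed, but to a similar extent in every arm. The session records keep the fine detail for WB-EMS.
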